#### Secondary analysis

In each cluster, we will collect relevant data from the local government to determine rates of reported local crime and level of engagement in civic affairs. Individual-level data in a multilevel/hierarchical regression modelling technique will take into account group characteristics.

*Planned subgroup analysis and reporting* include a focus on the gender of the offspring. Age of the traditional midwife is also of interest because it is a core issue in the recovery of traditional healing and care practices.

The statistical analysis of data will rely on CIETmap, an open-source interface with the R programming language [49].

### Economic analysis

The economic dimension is not trivial. Intercultural dialogue can lead to new solutions for health promotion based on adequate use of local resources [50]. Evaluation of the work of traditional midwives should recognise that far fewer official resources support their work than support Western-trained birth attendants. Finally, cultural loss and depletion of natural resources around indigenous communities mean that some authentic traditional midwives cannot work at full capacity and in these cases we may need to implement some actions to strengthen traditional health systems or at least take into account this imbalance in the measurement process.

In 2 years, the intervention might change some population-based maternity outcomes, allowing aggregated costs to be compared between intervention and control municipalities. The concern is to quantify the somewhat increased cost of adding the intervention and the much-increased access this affords to indigenous women. A starting point is an assessment of site-specific maternal health services available to indigenous women from a societal perspective, based on (1) the implementation costs of these services and (2) the implementation costs of the Safe Birth and Cultural Safety project. Site visits and in-person interviews with representatives of services and of the project will assess local implementation costs. We will measure costs in Mexican pesos and convert into US$ to allow for international comparison.

From the results of the final survey, we will identify direct benefits in terms of maternal mortality and morbidity indicators, particularly birth complications. Additional benefits we expect to evaluate are (1) change in access/uptake of services and (2) secondary effects like increases in social capital, health literacy, or community planning skills in maternal health services. Finally, we will identify the completeness and timing of implementation to provide a context. We will express the relation between benefits and differences in costs using cost-effectiveness ratios [51].

A third component of the economic analysis will project the costs and effectiveness of implementing the project using alternative models of intervention to enhance sustainability. The specific objectives of this component will be to predict the most cost-effective strategy for wider implementation of Safe Birth and Cultural Safety. It will also help to identify the resources (including local government funding and community participation) needed for rollout.

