**Discussion:**

Indigenous women at the periphery of Western health services do not benefit fully from the attenuated services which erode their own healthcare traditions. Western health service providers in indigenous communities often ignore traditional knowledge and resources, inadvertently or in ignorance, disrespecting indigenous cultures. Improved understanding between midwives and the official healthcare system can contribute to more appropriate referral of high-risk cases, improving the use of scarce resources while lowering costs of healthcare for indigenous families.

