The surveys will use instruments tested during the pilot study and will include questions about: maternal deaths, neonatal deaths, number of times women are seen by the traditional midwife during pregnancy, proportion of births at home attended by midwives or without external assistance, frequency of recourse to the traditional midwife in case of pregnancy complications, frequency of recourse to the traditional midwife in case of complications with newborns, proportion of women intending to have future births at home, infection postpartum, and cost of birthing. Among women who gave birth in health institutions, we also will ask questions about their treatment, including birth position, availability of translators, presence of family members at the birth, presence of the traditional midwife at the birth, bathing in cold water, treatment of the placenta, retention of amulets, and how respectful they consider their treatment to have been.

Secondary outcomes measured in the follow-up survey will include: prevalence of violent acts towards pregnant women, opinion as to whom the woman should consult first when she learns that she is pregnant, opinion of who should attend to the woman first if she has complications during pregnancy, opinion as to who should decide whether to take the woman to the hospital if there are complications during childbirth, perception of neighbours’ preferences as to who should provide antenatal care, perception of neighbours’ preferences as to home vs institutional birth.

A qualitative mid-course peer evaluation using the Most Significant Change technique with local stakeholders will provide information about progress and the relevance of secondary outcomes regarding cultural safety [47]. This technique is a participatory method for monitoring and evaluation of complex projects in which participants narrate stories describing the most significant changes they attribute to the intervention, and implementers review the stories. This will provide information about change dynamics, identify issues in implementation and provide moral support for the intercultural brokers*.*

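### The economic analysis is labelled societal, but the only cost inputs it names are those of the health services and the project

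*Protocol article*

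**What the plan says.** The Economic analysis section of the protocol article sets the perspective and the cost basis in one sentence: the assessment is made "from a societal perspective, based on (1) the implementation costs of these services", followed by the second item, "2) the implementation costs of the Safe Birth and Cultural Safety project". The next sentence fixes the source of these costs: "Site visits and in-person interviews with representatives of services and of the project will assess local implementation costs".

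The survey appears in that section on the benefit side only: "From the results of the final survey, we will identify direct benefits in terms of maternal mortality and morbidity indicators, particularly birth complications". The list then continues: "Additional benefits we expect to evaluate are (1) change in access/uptake of services and (2) secondary effects like increases in social capital", with health literacy and planning skills as further examples. Benefits and cost differences are to be combined in cost-effectiveness ratios.

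Two other places bear on household costs. Under Outcome measures, the content of the surveys includes "infection postpartum, and cost of birthing". The Discussion part of the abstract names, among the things that better understanding between midwives and the health system can bring, "lowering costs of healthcare for indigenous families".

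**The concern.** A societal perspective takes in costs whoever bears them, including families. The two inputs named here are borne by providers and by the project, and the informants named are on those two sides as well. The label and the stated content therefore do not match.

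This matters for the third specific objective, which is to evaluate the economic cost of the intervention. Household spending is a plausible place for the arms to differ. The article describes a long journey to the nearest facility for women in remote parts of the control municipalities, and its theory of change expects more use of midwives by women who do not need specialist care. A reader of the final ratio would take the societal label to mean that such costs had been counted.

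**Working it through.** The plan states no cost, saving or ratio, so there is no figure to reproduce. The check sets the statements side by side.

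| Element | Where | What is stated |
|---|---|---|
| Perspective | Economic analysis | Societal |
| Cost input 1 | Economic analysis | Implementation of the maternal health services |
| Cost input 2 | Economic analysis | Implementation of the project |
| Cost informants | Economic analysis | Representatives of services and of the project |
| Role of the final survey | Economic analysis | Mortality, morbidity and birth complications as benefits |
| Third component | Economic analysis, last paragraph | Projected costs and effectiveness of alternative models, and resources for rollout |
| Survey cost item | Outcome measures | Cost of birthing |
| Expected family gain | Abstract, Discussion | Lower healthcare costs for families |

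No row of the Economic analysis section names household spending, travel or time, and none gives the survey's cost item a role.

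The consequence can be written out. Let ΔS, ΔP and ΔH be the differences between arms in service cost, project cost and household-reported cost, and let ΔF be the difference in household payments to facilities that are already contained in S.

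- Cost difference from the named inputs: ΔS + ΔP
- Cost difference under a societal perspective: ΔS + ΔP + ΔH − ΔF
- Part left out: ΔH − ΔF

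The documents give no value for S, H or F, so the part left out cannot be sized. Its sign is also open. More births with a nearby midwife could lower family costs. More referrals to distant facilities, which the article also expects, could raise them.

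The one project cost that can be calculated is the stipends: 30 midwives × (US$20 + US$10) × 12 months = US$10,800 a year, or US$21,600 over two years. The sample size section gives 1,438 births per cluster with two clusters per arm, which is 2 × 1,438 = 2,876 in the intervention arm, but does not say whether that is one year or the whole period. If one year, stipends come to 10,800 / 2,876 = US$3.76 per birth. If two years, they come to 21,600 / 2,876 = US$7.51. Broker training and the staff workshops are extra and have no price in the article. These figures describe one piece of ΔP and say nothing about ΔH.

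**The case against.** The strongest reply is that a journal article condenses the plan and that the costing is introduced only as a beginning: "A starting point is an assessment of site-specific maternal health services available to indigenous women from a societal perspective". A full list of cost items may sit in another document. It can also be said that the third objective concerns the cost of the intervention, which the two named inputs serve.

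Part of this stands. A reader might infer that household costs are deliberately excluded. The text does not say so; it leaves room for further items and names none. What remains is a mismatch between a stated perspective and a stated cost basis, which is more than missing detail.

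Three further inferences go beyond the documents:

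- **That the trial cannot show family savings.** The cost of birthing is asked in surveys that could be compared between arms outside the ratio, although no such comparison is stated. The limit applies to the ratio as described.
- **That the trial claims family savings as a result.** The abstract words them as something that better understanding can contribute to. They are neither an objective nor a hypothesis.
- **That the incremental cost would have the wrong size or sign, because a modest family saving would cancel the project cost.** No household cost is given. The stipend arithmetic depends on an unsettled birth count and omits training and workshops, so offsetting the stipends would not offset the project.

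The survey item also has limits. That it means the household's own cost is inferred from its being asked in a household survey, and its coverage of travel or lost work is not stated.

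**Conclusion.** The point holds as a mismatch of label and content. The article declares a societal perspective, but every cost input it names belongs to the services or the project, and the surveys enter the economic analysis only for benefits. Followed as written, the ratio would be a provider and programme result called societal. The conclusion rests on the ordinary meaning of a societal perspective and on reading the survey item as a household cost. No magnitude or direction can be attached to it from the documents. The primary outcomes and the non-inferiority analysis are unaffected; the third objective is what the correction protects.

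**What to change.** Amend the Economic analysis section in one of two ways.

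1. **Keep the societal perspective.** Add the household-reported cost of birthing from the survey to the service and project costs. Where a payment to a facility is already in the service cost, count it once. Report the provider and programme result alongside as a second perspective. State that travel and lost time are covered only if the survey item includes them; if it does not, say that the household component is partial.
2. **Keep the two named inputs.** Relabel the perspective as provider and programme, and draw no conclusion on family savings from the ratio.

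The first option needs a few sentences and no new data collection for the birthing-cost item. Its price is that self-reported costs are noisier and may be incomplete, and that payments have to be separated enough to avoid double counting. The second option costs only wording, but gives a narrower answer.

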### Objectives

The overall objective is to reduce maternal morbidity and mortality in indigenous communities without further marginalising or undermining their cultures. The overall hypothesis is that recovery and strengthening of traditional healthcare have a positive impact on indigenous people’s health. An explicit intention is to develop an intercultural approach that reduces the dependence on external resources and promotes the cultural assets of indigenous communities.

Specific objectives of the study are: (1) to assess the impact on maternal health outcomes of a co-designed intervention to support traditional midwives in four municipalities of Guerrero; (2) to assess the secondary or social outcomes of this intervention, including gender violence against pregnant women and behaviours related to traditional midwives; and (3) to evaluate the economic cost of the intervention.

Research question: Among the four main indigenous groups in Guerrero, does support for authentic traditional midwives lead to non-inferior maternal health outcomes and improved social outcomes within the study period, when compared with usual care?

Theory of change: Intercultural brokers increase effective contact with Western health services; this improved referral generates better maternal outcomes by allowing obstetric attention to focus on those who need it most. Better maternal outcomes, along with the apprentices and economic support provided by the intervention, increase prestige of traditional midwives within the communities. Midwives’ prestige promotes cultural continuity and strengthens the social fabric. Additionally, this prestige expands their services among women who do not need specialist obstetric intervention, thus decreasing pressure on poorly funded healthcare services. The no-longer-overloaded healthcare services are then better able to deal with emergency cases and those in need of Western obstetric care, which further improves maternal outcomes.

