### Sample size calculation

Borrowing from the field of bioequivalence, equivalency trials and their statistical testing procedures focus on non-inferiority margins [53]. We expect that supporting traditional midwives does not result in worse primary outcomes of maternal health than does the available usual care in the region, principally because so few indigenous women in the study area access available services. Under the non-inferiority hypothesis, the trial might show equivalent or superior effects of the intervention [54]. The pilot study suggested additional benefits that secondary outcomes accrue from a culturally safe intervention. In the absence of previous studies in similar settings, we established a practical margin for non-inferiority-based discussion of findings with local authorities and indigenous communities. The resulting computation of study power illustrates the possibilities of demonstrating non-inferiority in these small communities of fixed size.

Based on 2013 data, we expected 5752 births across the four municipalities [55]. This study size is too small to use maternal mortality as an outcome over the funded duration of the trial, using 150% as the minimum non-inferiority margin to be detected. For birth complications as primary outcome, this study size can detect differences within a practical margin for non-inferiority of 15%, with 80% power at a significance level of 5% (Fig. 4).

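### Cost-effectiveness ratios are the only stated economic summary, yet their leading denominator is an outcome where equivalence counts as success and only four municipalities are randomised, so the ratio may be unreadable

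*Protocol article*

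**What the plan says.** The Economic analysis section of the protocol article gives one way of combining costs and effects: "We will express the relation between benefits and differences in costs using cost-effectiveness ratios". The effects come first from "direct benefits in terms of maternal mortality and morbidity indicators, particularly birth complications", and then from "1) change in access/uptake of services and (2) secondary effects like increases in social capital, health literacy, or community planning skills". The section describes its purpose as weighing "the somewhat increased cost of adding the intervention and the much-increased access this affords to indigenous women". Costs are to be compared in aggregate between intervention and control municipalities.

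Under Objectives, the research question asks whether the intervention will "lead to non-inferior maternal health outcomes and improved social outcomes within the study period". Under Sample size calculation, the authors write "We expect that supporting traditional midwives does not result in worse primary outcomes of maternal health", and add that "the trial might show equivalent or superior effects of the intervention". Under Random allocation of the intervention, two of four municipalities receive the intervention. The Principal analysis section counts 80 communities.

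**The concern.** A cost-effectiveness ratio divides the cost difference by the effect difference. For the leading effect measure, birth complications, one result the trial would count as a success is a difference close to zero. The ratio can then take very large values of either sign through chance alone. A negative ratio is ambiguous: it arises when the intervention costs less and averts complications (dominant), and also when it costs more and causes them (dominated).

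Two neighbouring effect measures are more exposed. Maternal mortality is listed as a direct benefit, but the Sample size section says the study is too small to use it as an outcome. Pregnancy complications, a primary outcome in the abstract, were almost equal in the pilot: 24/94 = 25.5% against 65/252 = 25.8%.

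The third specific objective is economic, and the section goes on to seek the most cost-effective strategy for wider implementation. A ratio that cannot be ordered is a poor headline for that purpose.

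**Working it through.** **The plan's own figures.** The economic section states no number. The nearest figures are in the Sample size section, for skilled attendance. 5752/4 = 1438 births per municipality and (97.8 − 92.1)/92.1 = 6.2% both reproduce. The stated 80% power does not match any closed form tried:
- 0.011 as a between-cluster coefficient of variation k: 99.8% (normal), 92% (cluster formula with one extra cluster per arm) or 69% (t, 2 df).
- 0.011 as an ICC: 68% (normal) or 29% (t, 2 df).

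The authors used a simulator and do not define the k-statistic, so both readings are carried below. Nothing here rests on the 80%.

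**When the ratio has a finite interval.** A 95% Fieller set for R = ΔC/ΔE contains every R with (ΔC − RΔE)² ≤ t²·Var(ΔC − RΔE). It is a finite interval only if |ΔE|/SE(ΔE) > t. The probability of a finite interval is therefore the power of the two-sided 5% test on ΔE, whatever the costs are.

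**Inputs.** Control rate p₀ = 57/248 = 23.0% and pilot intervention rate 9/91 = 9.9%, a difference of 13.1 points. Births per arm N = 2 × 1438 = 2876. Applying 0.011 to birth complications is an assumption, since it is given for skilled attendance.

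**Standard errors**, with v = [p₀(1−p₀) + p₁(1−p₁)]/N:
- A, 80 communities, ICC 0.011: √(v × [1 + (71.9 − 1) × 0.011]) = √(v × 1.780); t on 78 df = 1.99.
- B, four municipalities, 0.011 as k: √{([p₀(1−p₀) + p₁(1−p₁)]/1438 + 0.011² × (p₀² + p₁²))/2}; t on 2 df = 4.30.
- C, four municipalities, 0.011 as ICC: √(v × [1 + 1437 × 0.011]) = √(v × 16.807); t on 2 df = 4.30.

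At the pilot effect, √v = √((0.1770 + 0.0891)/2876) = 0.96 points. The standard errors are 1.28 (A), 0.98 (B) and 3.94 (C) points, and ΔE/SE is 10.2, 13.3 and 3.3.

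**Probability of a finite interval (noncentral t):**

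| True difference | A | B | C |
|---|---|---|---|
| 0 | 5% | 5% | 5% |
| 2 points | 27% | 19% | 6% |
| 3 points | 54% | 34% | 7% |
| 5 points | 94% | 66% | 11% |
| 13.1 points (pilot) | about 100% | about 100% | 45% |
| Skilled attendance, 92.1% to 97.8% | about 100% | 69% | 29% |

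With 500 births per arm (an assumption), the pilot row becomes about 100%, 80% and 38%.

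**Sign of the effect difference.** At a true difference of 0 the sign is a coin toss. At a true 1-point benefit the standard errors are 1.47, 1.13 and 4.51 points. The chance of the wrong sign is Φ(−0.68) = 25%, Φ(−0.89) = 19% and Φ(−0.22) = 41%.

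**The case against.** A reader might infer that the trial expects a difference near zero, with equality as its planning case, so that the ratio will usually have no finite interval. The documents do not support that. A non-inferiority hypothesis does not forecast equality, and superior effects are allowed for. The theory of change under Objectives says that "this improved referral generates better maternal outcomes by allowing obstetric attention to focus on those who need it most". The pilot, although not powered for effect, saw 9.9% against 23.0% birth complications. The 5% row of the table only restates the test level at a true difference of zero.

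Nor are birth complications the only denominator. The section speaks of ratios in the plural and lists access and uptake, where it expects a large change. Those ratios are less exposed than one whose denominator is near zero, though with four municipalities even the planned gain in skilled attendance gives a finite interval in only 29% to 69% of trials.

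Three further points stand. The article promises no interval for the ratio, and an uncertainty method may sit in a fuller plan, so its absence is not a fault. The Principal analysis already reports risk differences with intervals, and nothing prevents the authors from stating dominance when they report. The third objective, to evaluate economic cost, can be met without a usable ratio, and the projection of alternative models is not said to rest on it.

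The objection does not remove the point that the only combined summary named is one that can fail under a result the trial accepts as success.

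**Conclusion.** The point holds in conditional form, as a cheap improvement and not as an error in the plan. If the difference in birth complications is small or imprecise, a cost per complication averted will be unstable and its sign hard to read. At a true difference of 2 to 3 points, a finite interval occurs in 27% to 54% of trials over 80 communities and 6% to 34% over four municipalities. At the pilot difference the concern largely disappears over 80 communities (about 100% finite). Over four municipalities it depends on what 0.011 means: about 100% as a coefficient of variation, 45% as an ICC. Some of the exposure therefore comes from having few randomised units, and not only from the non-inferiority aim. The figures assume 2876 births per arm, a 23.0% control rate, and that 0.011 carries over from skilled attendance to birth complications.

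**What to change.** In the Economic analysis section, replace the ratio as the sole summary with the following:

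1. Report incremental cost and incremental effect separately, each with an interval that reflects allocation by municipality.
2. Show the two jointly on the cost-effectiveness plane.
3. Use incremental net benefit, over a stated range of values per complication averted, as the main summary.
4. Keep the ratio as a supplementary figure and name its quadrant (dominant, dominated or trade-off). Do not use it as the summary when the interval for the effect includes zero.

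This needs a change of wording and a small change of analysis, using data already planned. The drawback is that readers get results over a range of values instead of one headline ratio, and the range has to be chosen and justified.
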